## Background

Globally, major depressive disorder (MDD) is one of the most common psychiatric disorders, rated as one of the five leading cause of years lived with disability (YLDs) in 2016 and associated with substantial disabilities [1]. Patients with depression often show high suicide risk [2], severe impairments in social function [3] and cognitive dysfunction [4]. According to the 1995–1999 mortality data provided by the Minister of Health of the People’s Republic of China, the mean annual suicide rate was 23 per 100 000, and there were a total of 287 000 suicide deaths per year [5]. Therefore, it is especially important to quickly and effectively treat depression patients.

Electroconvulsive therapy (ECT) administered with anesthesia and neuromuscular blockers is the most effective treatment for depression [6–9]. However, the use of ECT is impeded by adverse effects (AEs), such as acute headache, dizziness and confusion [10], especially the cognitive function impairments, which may be affected by the stimulus intensity, number of treatments or electrode placement [11, 12]. Thus, researchers have been working on methods to quickly relieve symptoms while minimizing side effects.

One important feature of ECT is the rapid antidepressant effect in the early stage of treatment. Kellner et al. conducted a double-blind, controlled trial to compare the efficacy and cognitive effects of three electrode placement methods in ECT [13]. The results demonstrated that all placements resulted in rapid remission over the early course of treatment; during the first 3–4 ECT sessions, the bitemporal placement resulted in a more rapid decrease in symptom ratings than the other placements, followed by small changes in symptom ratings in the subsequent sessions for all placement groups. Some articles have reported that patients could go into remission after the first ECT session [14–16]. The findings indicated that the decline in symptom rating of later stage was not as rapid as the early period; furthermore, as the number of ECT sessions increased, the side effects became more pronounced [17], which suggests that we should change the mode of ECT procedure.

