Considering that patients with depression need quick symptom relief with few side effects, we propose a new two-step charge set strategy for ECT treatment, referred to as Hybrid-ECT. In Hybrid-ECT, conventional ECT is conducted during the first 3 sessions (the first step) because according to Kellner’s research, the Hamilton Rating Scale for Depression (HAMD-24) score reduction trajectory is steep during the first 3 ECT sessions (an approximation based on Figure 2 of Kellner’s article [13]), and then LCE is conducted until the treatment is terminated (the second step). We hope that the two-step Hybrid-ECT could combine ECT’s strength of an early rapid antidepressant effect and LCE’s advantage of fewer side effects. Therefore, our hypotheses were as follows: 1) Hybrid-ECT exerts a noninferior antidepressant effect relative to ECT over the whole course of the treatment; and 2) compared with the routine ECT charge set strategy, Hybrid-ECT may cause fewer AEs, especially in the later part of treatment (i.e., after 3 ECT sessions). To test these hypotheses, we designed the present randomized, double-blinded, parallel-group, controlled clinical trial. Since the intervention arm of this trial is a change in the current ECT charge setting strategy, routine ECT was selected as the standard-control group; and the trial is designed as a noninferiority study on the antidepressant effects of Hybrid-ECT and ECT.

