#### AEs

Any untoward medical occurrence during ECT/Hybrid-ECT treatment, which may or may not be causally linked with the ECT/LCE treatment, will be defined as an AE. All AEs will be recorded in the CRF. An important focus of this trial is to explore whether there are fewer side effects from Hybrid-ECT than from routine ECT, in addition to comparing total AE numbers and severity; therefore, all AEs will be categorized according to when they occurred (initial three ECT sessions or the subsequent ECT/LCE sessions) for further analyses.

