## Discussion

### Summary

To the best of our knowledge, this is a completely novel energy set strategy for ECT procedures. We speculate that Hybrid-ECT may rapidly relieve depressive symptoms during the early stage, then we will convert to LCE until the symptoms are completely relieved, and the side effects will occur less often than those in the control group (routine ECT). Furthermore, we will also perform the MRI and ERP assessments before and after the ECT treatment to test the hypothesis that Hybrid-ECT and routine ECT share the same antidepressant mechanisms. The strengths of the study include an innovative experimental design, time-intensive visits, detailed neuropsychological assessments, and MRI and ERP examinations to accurately document the differences in efficacy and side effects between Hybrid-ECT and ECT.

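### Later-phase adverse effect totals mix risk per session with the number of sessions received, so totals alone cannot show that LCE sessions cause fewer adverse effects than ECT sessions

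*Protocol article*

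**What the plan says.** The protocol article, under AEs, counts as an adverse effect "Any untoward medical occurrence during ECT/Hybrid-ECT treatment", whether or not it is causally linked. It plans the period split "in addition to comparing total AE numbers and severity", and states that "all AEs will be categorized according to when they occurred (initial three ECT sessions or the subsequent ECT/LCE sessions) for further analyses". No rate per session and no other exposure measure is given. Statistical analyses names a repeated-measures mixed model for continuous outcomes and chi-square or Fisher tests for categorical ones, in the modified intent-to-treat population. It does not single out adverse effect counts.

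The split serves the second hypothesis in the Background: "Hybrid-ECT may cause fewer AEs, especially in the later part of treatment (i.e., after 3 ECT sessions").

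The article gives no fixed or maximum number of sessions. In the Background, three conventional sessions are given "and then LCE is conducted until the treatment is terminated (the second step"). The Discussion (Summary) describes the course as "then we will convert to LCE until the symptoms are completely relieved". Withdrawal criteria removes a patient whose HAMD-24 falls by less than 3 points between the latest two visits. The Background also reports that "as the number of ECT sessions increased, the side effects became more pronounced".

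**The concern.** Both events that end a course, relief of symptoms and withdrawal for a small HAMD-24 change, depend on how the patient responds. If response over time differs between arms, so will the number of sessions after the third. An arm whose patients stop early then has fewer sessions in which adverse effects can arise, and an arm that needs longer courses has more, even when each session carries the same risk.

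The period split does not remove this. It settles sessions 1 to 3, where both arms follow the same energy setting and have the same nominal exposure. It leaves the later period, which has no common length.

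At stake is the reading of the second hypothesis. A lower later-phase total under Hybrid-ECT could mean gentler sessions or fewer sessions. An equal total could hide gentler sessions given more often. The article calls fewer side effects an important focus of the trial, so the result should be able to separate these.

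**Working it through.** **The plan's own figure.** There is none for adverse effects. The only sample size is for HAMD-24 change, and it reproduces. With margin 4, SD 8, one-sided alpha 0.05 and power 0.80 (Sample size and power calculation), n per arm = 2 × 8² × (1.645 + 0.842)² / 4² = 49.5, so 50. Then 50 / 0.9 = 55.6, so 56 per arm and 112 in total. The point below does not change it.

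**Inputs for the illustration.** From the article: 3 initial sessions in each arm, and about 50 patients per arm after drop-out. Assumed, because the article gives no values: 8 sessions in the ECT arm, 6 to 12 in the Hybrid arm, and 0.3 to 1.0 adverse effects per session.

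**Equal risk per session.** With S_H and S_E sessions per patient:
- ratio of whole-course totals = S_H / S_E
- ratio of later-phase totals = (S_H − 3) / (S_E − 3)
- ratio per session = 1.00 throughout

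The last three columns give the chance that an unadjusted two-sided 0.05 test on mean whole-course counts declares a difference. With r the rate per session, the standardised difference is r(S_H − S_E) / √[r(S_H + S_E) / 50].

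| Hybrid sessions (ECT = 8) | Total ratio | Later ratio | r = 0.3 | r = 0.5 | r = 1.0 |
|---|---|---|---|---|---|
| 6 | 0.75 | 0.60 | 0.544 | 0.762 | 0.966 |
| 7 | 0.875 | 0.80 | 0.170 | 0.252 | 0.447 |
| 8 | 1.00 | 1.00 | 0.050 | 0.050 | 0.050 |
| 10 | 1.25 | 1.40 | 0.447 | 0.654 | 0.915 |
| 12 | 1.50 | 1.80 | 0.934 | 0.994 | 1.000 |

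As an example, for 6 sessions and r = 0.3 the means are 1.8 and 2.4, the standard error is √(4.2 / 50) = 0.290 and the standardised difference is −2.07, giving 0.544. The calculation assumes Poisson counts and the same number of sessions for every patient in an arm. Extra variation between patients would lower these probabilities but would leave the ratios as they are.

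**A true 30% lower risk per later Hybrid session.** Later ratio = 0.7 × (S_H − 3) / 5; total ratio = [3 + 0.7 × (S_H − 3)] / 8.

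| Hybrid sessions | Total ratio | Later ratio |
|---|---|---|
| 6 | 0.64 | 0.42 |
| 8 | 0.81 | 0.70 |
| 10 | 0.99 | 0.98 |
| 12 | 1.16 | 1.26 |

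With 10 Hybrid sessions the benefit has almost vanished from the totals. With 6 it looks almost twice as large as it is (58% fewer against 30%).

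**A more modest case.** If 10% of one arm, the planned drop-out rate, lost all 5 later sessions and nobody in the other arm did, the later ratio at equal risk would be 4.5 / 5 = 0.90.

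**The case against.** The strongest reply is that totals answer a proper question. The trial compares two charge-setting strategies, and the number of sessions is a consequence of the strategy assigned. If Hybrid-ECT needs more sessions and so produces more adverse effects, patients bear that cost. This stands. Session count is not a confounder, and totals per patient are a valid measure of burden over the assigned course.

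A second reply is that exposure adjustment is ordinary analysis-plan detail, and that nothing in the article rules it out. This stands in part. The article fixes no test for adverse effects, but it does name totals as the comparison, and it links the hypothesis to a period of variable length.

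Third, a rate per session has weaknesses of its own. It conditions on staying in treatment and so gives up the full randomised comparison. The log of the number of later sessions is undefined for a patient with none. A constant-rate offset also sits uneasily with the article's statement that side effects grow with session number. All of this stands, and it is why the rate should accompany the totals and not replace them.

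Fourth, the hypothesis has other support: severity, orientation recovery at every session, and the cognitive battery. This also stands.

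A reader might infer that early failure of Hybrid-ECT will make it look safer. The documents do not show this. The withdrawal rule is the same in both arms, no imbalance in sessions is shown, and slower relief would lengthen Hybrid courses. The in-house finding of slower relief concerns the first few sessions of LCE, not LCE given after three ECT sessions.

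**Conclusion.** The point holds in a limited form. As written, a difference in later-phase totals is the product of risk per session and sessions received, and the split by period does not separate the two. Totals alone therefore cannot support the second hypothesis as a statement about LCE sessions against ECT sessions. They can support a statement about adverse effects over the assigned course.

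The size is unknown. The ratios of 0.60 and 1.40 at equal risk, and the rejection probabilities, rest on assumed session counts and rates. The 0.90 of the modest case shows that the distortion may be small. Its direction cannot be determined from the documents. It would be going too far to call the safety comparison invalid, or to say that it favours Hybrid-ECT.

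**What to change.** In AEs:
- Keep total adverse effects per patient as the measure of whole-course burden.
- Add a prespecified comparison of adverse effects per session from session 4 onward: a negative binomial model, or a Poisson model fitted by GEE, with the log of the number of later sessions as offset, among patients with at least one later session.
- Report beside it the distribution of session counts and the number of patients stopping by session 3, in each arm.
- State that a claim of fewer adverse effects after session 3 will rest on both measures.
- Note the limits of the rate: it is conditional on continuing treatment and assumes roughly constant risk per session.

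The cost is wording and analysis work. The rate needs only the planned two-period classification and a session count per patient. The article does not say that the count is recorded, but orientation recovery is assessed at every session, so it should be obtainable; confirm that the case report form captures it. The sample size stays at 112, and no change to treatment or withdrawal rules is implied.

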#### Sample size and power calculation

Only one study [21] has measured changes in depression symptom and cognitive effects between pre- and post-NET. Therefore, to test the first hypothesis, we used noninferiority tests [53] calculated using the Power Analysis and Sample Size Software (ver.15.0) (NCSS, LLC. Kaysville, Utah, USA) for the difference between two means (noninferiority margin = 4.0, standard deviation (SD) = 8.0, power = 0.8, a = 0.05 (one-tailed), drop-out rate = 10%) of the change in HAMD-24 scores with a 1:1 allocation, and we obtained a total sample size of 112 (56 for each arm).

### Statistical analyses

#### Neuropsychological and clinical outcomes

Demographic and baseline data will be analyzed using independent two-sample *t*-tests or chi-square tests (or Fisher’s exact tests). All analyses of clinical outcomes, neuropsychological results and safety indicators will be performed for the modified intent-to-treat population (MITTP) (at least one treatment and at least one postbaseline measure). We will use mixed-effects model repeated measures (MMRM) as the main analysis for the comparison of the primary and continuous secondary outcome measures. We will use chi-square/Fisher’s exact tests to analyze the categorical outcome measures. We will use a “tipping point” analysis to assess the robustness of the primary analysis (MMRM) to possible deviations from the missing at random (MAR) assumption. The significance level will be set to 0.05 (two tailed). All statistical analyses will be performed with SAS (ver. 9.4) software (SAS Institute Inc., Cary, NC, USA). MRI and ERP data analyses will be performed by using the relevant professional software packages (FreeSurfer [54], FSL [55], EEGLAB [56], etc.*)*.

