#### MRI protocol

MRI will be performed at 3 time points: t_0_ (~ 24–48 h before baseline), t_1_ (~ 24–48 h after the three first ECT and before the fourth ECT/LCE) and t_5_ (~ 7 days the last of ECT/LCE). All participants will be scanned at the Shenzhen Kangning Hospital Neuropsychiatry Imaging Center in a 3 T Discovery MR750 scanner (GE Healthcare, Milwaukee, USA) equipped with an eight-channel head coil. A standard MRI protocol will be applied at each time point, including a T1-weighted spoiled gradient echo, SPGR (TE = min full; TR = 6.7 ms; flip angle = 12°; field of view =256 mm; voxel size = 1.0 * 1.0 * 1.0 mm^3^; matrix = 256 * 256); a T2-weighted high resolution hippocampus sequence (TE = 50 ms; TR = 8020.0 ms; flip angle = 122°; field of view =175 mm; voxel size = 0.4 * 0.4 * 2.0 mm^3^; matrix = 448 * 448); a resting-state fMRI scan with a BOLD sequence (TE = 25 ms; TR = 2000 ms; field of view =220 mm; voxel size = 3.4 * 3.4 * 3.2 mm^3^; matrix = 64 * 64; volume number = 240); a DTI sequence (TE = 81.4 ms; TR = 8724.0 ms; field of view = 224 mm; voxel size = 2.0 * 2.0 * 2.0 mm^3^; matrix = 112 * 112; number of diffusion directions = 64; b values = 0, 1000 s/mm^2^); ^1^H- magnetic resonance spectroscopy (MRS) sequences for the ROIs including the hippocampus, thalamus, anterior cingulate and posterior cingulate (TE = 35.0 ms; TR = 1500 ms) [44–46]; and a 3D ASL sequence (TE = 10.5 ms; TR = 4389 ms; post-labeling delay = 1025 ms; field of view =240 mm).

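### Safety is analysed in a set that requires a postbaseline measure, so a treated patient who stops before any such measure is left out of the safety analysis

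*Protocol article*

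**What the plan says.** Under Statistical analyses, the paragraph on neuropsychological and clinical outcomes uses one population for everything. Its subject is "All analyses of clinical outcomes, neuropsychological results and safety indicators", and the population is the MITTP, which needs both a treatment and a later measure: "safety indicators will be performed for the modified intent-to-treat population (MITTP) (at least one treatment and at least one postbaseline measure"). No separate set of treated patients is named for safety, and the article does not say what counts as a postbaseline measure.

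The AEs section is wider. An AE is "Any untoward medical occurrence during ECT/Hybrid-ECT treatment", with no condition that a rating follows. It also states "All AEs will be recorded in the CRF". The purpose is plain: "An important focus of this trial is to explore whether there are fewer side effects from Hybrid-ECT than from routine ECT". The section promises that the arms will be compared on how many AEs occur and how severe they are. Every AE is then to be "categorized according to when they occurred (initial three ECT sessions or the subsequent ECT/LCE sessions").

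**The concern.** The two sections do not fit together. One records every AE in treated patients and promises to compare them. The other admits to the safety analysis only patients who stayed long enough to be measured. A patient who has a bad reaction at the first or second session and stops has been treated and has an AE on file, yet may have no postbaseline measure. Membership of the safety set then depends partly on the outcome that the set is meant to measure.

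Fewer side effects is the second of the trial's two hypotheses, so the AE tables carry weight. What is at stake is the absolute frequency and severity of AEs in the first three sessions, above all events that end treatment.

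**Working it through.** **The plan's own figure.** The sample size is not disputed; it supplies the denominator used below. From Sample size and power calculation: margin 4.0, SD 8.0, one-sided alpha 0.05, power 0.80, dropout 10%. With a true difference of zero, n per arm = 2 × (1.645 + 0.842)² × 8² / 4² = 49.5, rounded up to 50. Then 50 / 0.9 = 55.6, rounded up to 56, or 112 in total. This matches the article.

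**Who can be lost.** The patient must have had at least one session, because untreated patients are removed separately under Randomization, and must have no postbaseline measure. Two readings of the undefined term give different answers.

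- *The per-session orientation test counts.* Under Neuropsychological assessment it is done at every session, and a patient who has not regained orientation is scored 100 min. Failure to recover therefore yields a value, not a gap. Only a patient in whom the test was never attempted would be lost, so almost none.
- *A clinical rating is meant.* The earliest postbaseline visit that can be timed from the text is t1, which the MRI protocol places "after the three first ECT and before the fourth ECT/LCE". Table 1, with the rating schedule, is not shown. If the first rating falls at t1, patients who stop after session 1 or 2 without a rating are lost.

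**Size, on assumed counts.** The documents give no AE rates, so these are illustrations. Let 56 patients be treated in an arm, x of them have an AE and no postbaseline measure, and the other 56 − x have AE rate p. The MITTP reports p. The rate in all treated patients is [p(56 − x) + x] / 56, so the understatement is x(1 − p) / 56.

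| p (MITTP) | x = 1 | x = 3 | x = 6 |
|---|---|---|---|
| 20% | 21.4% | 24.3% | 28.6% |
| 40% | 41.1% | 43.2% | 46.4% |
| 60% | 60.7% | 62.1% | 64.3% |

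The understatement runs from 1 × 0.4 / 56 = 0.7 points to 6 × 0.8 / 56 = 8.6 points. Each lost patient costs between 0.4 / 56 = 0.7 and 0.8 / 56 = 1.4 points. The x = 6 column is an upper bound: the whole dropout allowance is 10% × 56 = 5.6 per arm, for all causes and at any time.

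For a rarer class of event the relative effect is larger. If 6 of 56 patients have a severe AE (10.7%) and 1 leaves unmeasured, the reported rate is 5/55 = 9.1%. If 3 leave, it is 3/53 = 5.7%, but 3 would already use more than half of the 5.6.

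**Effect on the comparison of arms.** With x1 and x2 lost and the same p in both arms, the difference between arms shifts by (x1 − x2)(1 − p) / 56. The Hybrid-ECT Stimulus section gives the first three sessions the same energy setting as in the control arm, and assignment is blinded, so x1 and x2 should be equal in expectation. A chance split of 3 against 1 at p = 20% would shift it by 2 × 0.8 / 56 = 2.9 points. Patients lost before session 4 have no session-4-or-later events to contribute under either set.

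**The case against.** The strongest reply is that the rule may exclude almost nobody. The orientation test is done at every session, non-recovery is scored, and the section on safety assessment lists cognitive assessments among the safety data. On that reading the MITTP is close to the set of all treated patients. This stands as a limit on the size. It does not rescue the rule: the term is undefined, and a condition that excludes nobody is not needed for safety, while one that excludes somebody excludes patients whose AEs should be counted.

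A second reply is that safety indicators may mean only laboratory tests, ECG and similar measurements, with AEs handled apart under their own heading. The text does not settle this. Including AEs is the likelier reading, because safety assessment and AEs share a heading and no other population is named for AEs.

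A reader might go further and infer that patients who stop early because of an AE generally disappear from the AE comparison, or that the result is tilted towards Hybrid-ECT. The documents do not support either. Those who stop after their first postbaseline measure stay in. Early losses should be balanced, because the energy setting is the same in both arms up to session 3. The second hypothesis looks mainly to the period after session 3, which is little affected. Nor does the AEs section make the first three sessions a reference for the later ones; it only sorts AEs by period.

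An unseen statistical analysis plan does not remove the point, because the article states a population for safety and does not leave the choice open.

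**Conclusion.** The point holds in a limited form. The article places safety in a population that requires a postbaseline measure, which can leave out treated patients with a recorded AE and conflicts with the promise to compare all AEs. The likely consequence is some understatement of absolute AE rates in sessions 1 to 3: close to nil if the per-session orientation test counts, and about 0.7 to 1.4 percentage points per lost patient in an arm of 56 if it does not.

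These sizes assume background AE rates of 20% to 60%, an AE in every lost patient, and a first rating no earlier than t1; none of these can be checked in the article. No systematic bias between arms is expected, though a chance imbalance of a few patients could move the early-session comparison by a few points. The sample size is unaffected.

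**What to change.** In the paragraph on neuropsychological and clinical outcomes, separate the two sets. Keep the MITTP for efficacy and neuropsychological outcomes. Analyse AEs and safety indicators in all randomised patients who received at least one ECT or LCE session, with no postbaseline-measure condition, and use that set for both AE periods.

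The cost is one sentence. No new data are needed, because AEs are already recorded on the case report form, and the total of 112 does not change. Reported AE rates may become slightly less favourable.

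### The noninferiority test is sized at one-sided 0.05, but the analysis section sets 0.05 two-tailed with no exception for the primary outcome

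*Protocol article*

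**What the plan says.** The Background states the first hypothesis as noninferiority: "Hybrid-ECT exerts a noninferior antidepressant effect relative to ECT over the whole course of the treatment". The section on sample size and power calculation sizes the trial for that hypothesis with a noninferiority test on the change in HAMD-24. Its inputs are "noninferiority margin = 4.0", "standard deviation (SD) = 8.0" and "power = 0.8, a = 0.05 (one-tailed), drop-out rate = 10" percent, and it concludes "with a 1:1 allocation, and we obtained a total sample size of 112 (56 for each arm").

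Under Statistical analyses, the section on neuropsychological and clinical outcomes makes an MMRM the main analysis for the primary outcome and for the continuous secondary outcomes. The population is modified intent-to-treat: patients treated at least once and assessed at least once after baseline. Baseline comparisons and categorical outcomes are dealt with in the same paragraph. One level is then given for all of it: "The significance level will be set to 0.05 (two tailed"). The primary outcome is not set apart, and the margin of 4.0 is not mentioned again.

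**The concern.** A noninferiority test at one-sided 0.05 corresponds to a two-sided 90% interval. Holding the same comparison to two-tailed 0.05 corresponds to a two-sided 95% interval, which is one-sided 0.025 against the margin. These are different tests with different error rates and different power, and the article states both levels without saying which one applies to the primary comparison.

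The first hypothesis is the one the trial was sized for. With two levels in print, the same data could be declared noninferior under one and not under the other. If the choice is left until results are known, it could decide the conclusion. The quoted 80% power is also tied to only one of the two levels.

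**Working it through.** **Inputs.** From the section on sample size and power calculation: margin 4.0, SD 8.0, power 0.80, one-sided alpha 0.05, dropout 10%, 1:1 allocation. From the analysis section: 0.05 two-tailed. The true difference is not stated; 0 is assumed because it reproduces the stated total.

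**Step 1: reproduce the plan's figure.**

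n per arm = 2 × (1.645 + 0.842)² × (8/4)² = 49.5, rounded up to 50.

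Allowing for dropout: 50/0.9 = 55.6, rounded up to 56 per arm, 112 in total. This matches exactly, so the sizing did use one-sided 0.05. (A noncentral-t calculation gives 51, then 57 per arm, 114 in total.)

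**Step 2: power of the same design at each level.**

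Standard error with 50 per arm = 8 × √(2/50) = 1.6, and 4/1.6 = 2.5. With 56 per arm, 8 × √(2/56) = 1.512, and 4/1.512 = 2.646. Power = Φ(margin/SE − z).

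| Evaluable per arm | One-sided 0.05 (z = 1.645) | Two-tailed 0.05 (z = 1.96) |
|---|---|---|
| 50 | 0.804 (t: 0.799) | 0.705 (t: 0.697) |
| 56 | 0.842 (t: 0.838) | 0.754 (t: 0.746) |

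**Step 3: what 80% would take at the two-tailed level.**

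n per arm = 2 × (1.96 + 0.842)² × (8/4)² = 62.8, rounded up to 63; 63/0.9 = 70 per arm, 140 in total. This is given for scale only.

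**Step 4: where the two rules disagree.**

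With SE 1.6, the 95% rule passes if the observed deficit of Hybrid-ECT is below 4 − 1.96 × 1.6 = 0.86 points. The 90% rule passes if it is below 4 − 1.645 × 1.6 = 1.37 points.

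The verdict therefore differs for observed deficits between about 0.86 and 1.37 points. If the arms are truly equal, the chance of landing there is Φ(1.37/1.6) − Φ(0.86/1.6) = Φ(0.855) − Φ(0.54) = 0.804 − 0.705, or about 10%.

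**The case against.** The best defence is that the specific statement should govern the general one. The sample size section ties one-tailed 0.05 expressly to the first hypothesis. The two-tailed sentence closes a paragraph that also covers baseline tests, categorical outcomes and the secondary measures. On that reading the noninferiority test keeps its 80% power and the analysis section lacks only an exception clause. This is a fair reading, and it is why the lower power can be stated only conditionally. It does not remove the contradiction, because the same paragraph covers the primary comparison by name and then sets one level.

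A second defence is that the MMRM can use partial data from patients who leave early, so 50 evaluable per arm may be pessimistic. This stands, and it is why the range runs up to about 75%. Any further gain in precision from the model cannot be quantified from the article.

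Two stronger readings are tempting, and the article supports neither. A reader might infer that the trial has no noninferiority rule. The hypothesis, the noninferiority test and the margin are all stated. Only the sentence naming the confidence bound is absent, and an article may leave that to the full protocol or analysis plan. A reader might also infer that a non-significant two-tailed difference will be taken as proof of noninferiority. Nothing in the article proposes that; it speaks of an MMRM comparison and, in the sizing, of noninferiority tests against a margin.

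**Conclusion.** The concern holds as an internal contradiction on the error rate of the primary noninferiority test. It does not show that the stated power is false outright.

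- If the two-tailed level governs, power is about 70% with 50 evaluable per arm and about 75% if all 56 contribute, against the stated 80%.
- If one-sided 0.05 governs, 80% stands and the two-tailed sentence is wrong for the primary outcome.

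The power figures rest on the plan's own SD of 8.0 and margin of 4.0, on an assumed true difference of 0, and on a simple two-mean comparison with no credit for MMRM precision. The practical window of disagreement is narrow, about half a HAMD-24 point, but it falls in the trial's main efficacy decision. An unseen analysis plan may settle the level; the published text would still state two.

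**What to change.** Before any outcome data are seen, state in the analysis section which level applies to the primary noninferiority test. State also that the upper limit of the matching confidence interval for Hybrid-ECT minus ECT in HAMD-24 change (higher = worse) is compared with 4.0. Either route reconciles the text:

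- **(a)** Use the two-sided 95% interval, and restate the power in the sample size section as about 70% with 50 evaluable per arm, rising to about 75% if all 56 contribute.
- **(b)** Use the two-sided 90% interval (one-sided 0.05), keep the 80%, and limit the two-tailed 0.05 level to the other outcomes.

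The change is one or two sentences and needs no additional patients. The price of (a) is a less favourable stated power. The price of (b) is a more lenient one-sided 5% error rate, stated openly.
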